### 3.11 Retrospective data collection for screen failures

For patients who are screened then deemed ineligible due to having X-ray changes of OM on baseline X-ray or due to clinician preference for no antibiotics, we will retrospectively audit their clinical outcomes at the conclusion of this trial. Patients identified between March 2024 and December 2025 will be included. Data will be assessed from date of screening till day 90 post-screening. We aim to look at the following data:

- a) Demographics
  - i. Age
  - ii. Sex
- b) Baseline ulcer size
- c) Wlfl score
- d) Serum inflammatory biomarkers
  - i. Total peripheral white cell count
  - ii. C-reactive protein

- e) Antibiotic therapy prescribed
- f) Clinical failure outcomes at 90 days (i.e. need for further antibiotics, need for surgery)
- g) Wound healing

## 4. Study population

### 4.1 Recruitment

All adult patients assessed to have with diabetic foot ulcers that probe to bone will be added to the screening log. Patients will be approached for consent when probe-to-bone test is determined to be positive. If not already performed within previous 72 hours, X-rays will be performed within 48 hours of consent. Eligibility will be assessed following review of the X-ray by a radiologist. Those who do not demonstrate radiological changes of osteomyelitis will then be considered eligible and included for randomization. Patients who do not meet eligibility criteria will be informed of their exclusion from the trial.

### 4.2 Inclusion criteria

- Adult patient (≥18 years) with diabetic foot ulcer
- Ulcer with positive probe-to-bone test
- X-ray performed within 72 hours of enrollment demonstrating no changes suggestive of osteomyelitis at the site of the ulcer by the reporting radiologist
- Willing and able to consent

### 4.3 Exclusion criteria

- Systemic antimicrobial therapy for >7 days in the 30 days prior to initial enrollment
- Systemic signs of sepsis based on SIRS criteria
- Initial surgical therapy deemed more appropriate than medical management alone of diabetic foot infection
- Treating clinician deems no antibiotic therapy required
- Known pregnancy

### 4.4 Consent

All eligible patients will be provided with a verbal explanation of the study, along with a paper consent form. A copy of the form may be given to patients if they would like to discuss further with treating medical team or family. Patient's competence and capacity to provide informed consent will be assessed by the recruiting investigator prior to the patient being recruited. Patients will be deemed competent if they:

1. Are able to comprehend and retain information relevant to making the decision;
2. Understand the information and implications of the decision
3. Are able to weigh the information and arrive at the decision

Consent may be obtained verbally via telephone if unable to get physical signature provided a witness (who is not a study investigator) also signs the consent form. Study investigators

will attempt to obtain a physically signed copy of the consent form at next physical review with the study participant where possible.

#### 4.4.1 Teletrial consent

For participants from a satellite site (i.e. Bendigo Health), along with the standard consent form, a stand-alone teletrial specific participant information and consent form will also be required to be signed. This consent form details the specifics of the teletrial model and will require participants to also consent for their data being collected for Australian Teletrial Program reporting.

### 5. Participant Safety and Withdrawals

#### 5.1 Risk Management and Safety

Given this is a pilot feasibility study with a relatively low number of planned participants, a data monitoring committee will not be established. Serious adverse events will be referred to two independent clinicians blinded to the intervention with experience in infectious disease and diabetic foot infections for adjudication.

#### 5.2 Handling of withdrawals

Participants in the study may withdraw at any point. An early termination will occur when an enrolled subject withdraws consent to participate in the study prior to the primary outcome assessment at day 90. Data collected prior to the participant's withdrawal will be included in the analysis.

#### 5.3 Replacements

Any withdrawals post randomization will not be replaced.

### 6. Statistical methods

#### 6.1 Sample size estimation and justification

This is a pilot trial, aiming to assess the feasibility and safety of short course therapy in diabetic foot ulcers with positive PTB and no X-ray changes of OM. This will also provide local estimates for power calculation in future trials.

We will recruit a total of 120 participants (60/group) as this will provide precise estimates of feasibility outcomes (with confidence interval of <20%). Such sample size will also provide a reliable estimate for future trials, as it has been shown that the gain in precision of binary outcome is smaller once each group reaches 60 participants.

Based on our local experience, we estimate approximately 3 patients per week present with positive PTB and normal X-rays. Assuming a 50% recruitment rate, this would result in 117 eligible patients in an 18 month period. Therefore the trial recruitment is likely to be completed within around 18 months.

#### 6.2 Statistical methods to be undertaken

Results will be presented according to CONSORT guidelines for feasibility studies. Data analysis will be conducted on an intention-to-treat principle alongside an additional per-protocol analysis.

Feasibility outcomes will be presented as percentage with 95% confidence intervals. Exploratory clinical outcomes and safety outcome will be presented as risk difference with 95% confidence intervals.

Amount and pattern of missing data will be explored.

## 7. Storage of Blood and Tissue Sampling

There will not be any additional storage of blood or tissue samples for the purposes of this trial. Patient samples will get processed as per standard hospital pathology protocol.

## 8. Data Security and Handling

Patient clinical details and demographics will be recorded on data collection forms on an electronic REDCAP database by investigators. The collected data will be stored in the REDCap database on password-protected computers. Patient level data will not be shared between participating sites.

Study related documents used in this study will be stored in a re-identifiable manner, with individual patient CRFs not containing any patient identifiers beyond a study ID. A site log will be maintained to identify participants to their study ID and their data at each site. This log will be locked in a secured password-protected file on the local hospital servers at each study site and not shared with other sites or the sponsor. All data for the study will be retained for a period of fifteen years after which all electronic and paper documents will be destroyed in accordance with hospital policy in place at the time.

## Appendix 1 – Schedule of events

|                            | Day 0 | Day 14 | Day 42 | Day 90 |
|----------------------------|--------------|---------------|---------------|---------------|
| Baseline data       | X            |               |               |               |
| Ulcer assessment    | x            | x             | x             | X             |
| X-ray               | x            | x             | X             |               |
| Blood tests         | x            | x             | x             |               |
| Outcome assessments |              | x             | x             | x             |

## Appendix 2 – Baseline data collection fields

|                           |                                                                                                                                                                                                                                                                                                                                                                                                                                                                                                                                                                                                                                                                                                                                                                                                                                                                                                                                                                                                                                                                                                                                                                                                                                       |
|---------------------------|---------------------------------------------------------------------------------------------------------------------------------------------------------------------------------------------------------------------------------------------------------------------------------------------------------------------------------------------------------------------------------------------------------------------------------------------------------------------------------------------------------------------------------------------------------------------------------------------------------------------------------------------------------------------------------------------------------------------------------------------------------------------------------------------------------------------------------------------------------------------------------------------------------------------------------------------------------------------------------------------------------------------------------------------------------------------------------------------------------------------------------------------------------------------------------------------------------------------------------------|
| Demographics       | 
 
• Sex (Male, female, other)
 
• Age (in years)
 
                                                                                                                                                                                                                                                                                                                                                                                                                                                                                                                                                                                                                                                                                                                                                                                                                                                                                                                                                                                                                                                                                                                               |
| Comorbidities      | 
 
• Diabetes type
 
• Diabetes duration (approximate, years)
 
• Macrovascular complications of diabetes
 
• Microvascular complications of diabetes
 
• HbA1c (%) within 90 days of enrolment
 
• History of previous foot ulceration
 
• History of previous amputation
 
• Extent of previous amputation
 
• Ankle-brachial pressure index (i.e. ankle systolic BP/brachial systolic BP)
 
• Systolic toe pressure measurement (mmHg)
 
• Smoking status
 
• Smoking duration (approximate, in pack years)
 
• Charlson Comorbidity Index Score
 
• Immunosuppression 
 
○ Solid organ tumour in past 5 years (yes/no)
 
○ Transplant recipient (yes/no)
 
○ Known human immunodeficiency virus (HIV) infection (yes/no)
 
○ Splenectomy/functional asplenia (yes/no)
 
○ Iatrogenic immunosuppression and type
 
 
 
                                                                                                                                                                                             |
| Initial assessment | 
Ulcer assessment
 
 
• Ulcer location 
 
○ Ulcer onset (approximate date of onset)
 
○ Precipitant of ulcer (trauma, pressure injury, iatrogenic, etc)
 
○ Recurrent ulcer (yes/no)
 
○ Ulcer measurement (maximum diameter and perpendicular diameter, mm)
 
○ Ulcer depth (mm)
 
 
 
 
Wifl score
 
 
• Depth grade 
 
○ Ischaemia grade
 
○ Infection grade
 
 
 
 
Systemic antibiotic therapy within last 30 days
 
 
• Duration of antibiotic therapy 
 
○ Antibiotic used
 
 
 
 
Microbiology results
 
 
• Wound swab collection (yes/no) 
 
○ Date of wound swab
 
○ Organisms identified
 
 
 
 
Serum biomarkers
 
 
• Baseline C-reactive protein (mg/L)
 
• Baseline peripheral white cell count (<math>\times 10^9/L</math>)
 
 |

### Appendix 3 – Medication adverse event assessment

| Adverse event category  | Adverse event and definition                                                                                                                                                                                                                                                             | Present at review (Yes/No) | Details |
|-------------------------|------------------------------------------------------------------------------------------------------------------------------------------------------------------------------------------------------------------------------------------------------------------------------------------|----------------------------|---------|
| Gastrointestinal | Diarrhoea: >3 loose stools per day associated with antibiotic administration in the absence of laxative or pre-existing enteritis                                                                                                                                                        |                            |         |
|                         | Nausea and vomiting: associated with antibiotic administration, in the absence of alternate explanation                                                                                                                                                                                  |                            |         |
| Haematologic     | Anaemia: Hb<100g/L                                                                                                                                                                                                                                                                       |                            |         |
|                         | Leukopenia: WCC < 4.0 x 10  /L                                                                                                                                                                                                                                               |                            |         |
|                         | Thrombocytopenia: platelet count <150 *10  /L                                                                                                                                                                                                                                |                            |         |
| Hepatobiliary    | Cholestasis: total bilirubin >21µmol/L                                                                                                                                                                                                                                                   |                            |         |
|                         | Transaminitis: AST or ALT >3 times patient's baseline                                                                                                                                                                                                                                    |                            |         |
| Renal            | Increase in serum creatinine >1.5 times patient's baseline                                                                                                                                                                                                                               |                            |         |
| Neurologic       | Altered mental status compared to patient's baseline                                                                                                                                                                                                                                     |                            |         |
|                         | Peripheral neuropathy                                                                                                                                                                                                                                                                    |                            |         |
|                         | Seizures                                                                                                                                                                                                                                                                                 |                            |         |
| Dermatologic     | Rash                                                                                                                                                                                                                                                                                     |                            |         |
|                         | Red-man syndrome                                                                                                                                                                                                                                                                         |                            |         |
| Cardiac          | QTc prolongation (>400ms in males or >460ms in females) on ≥2 ECG tracings                                                                                                                                                                                                               |                            |         |
| Anaphylaxis      | Generalised, rapidly progressing, multi-system IgE-mediated allergic reaction (symptoms include difficult or noisy breathing, swelling of the tongue, swelling or tightness in throat, difficulty talking or hoarse voice, wheeze or persistent cough, persistent dizziness or collapse) |                            |         |

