### 3.3 Intervention

Patients will receive 2 weeks of antibiotic therapy from date of index X-ray demonstrating no radiological evidence of osteomyelitis.

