### 3.5 Participant timeline

Total follow up period for participants will be 90 days from date of recruitment. In-person or Telephone/telehealth follow up will be conducted at 14 days (+/- 2 days), 42 days (+/- 2 days) and 90 days (+/- 5 days) from the date of recruitment.

Following recruitment, all patients will be randomized to either the intervention (2 weeks) or the control (6 weeks) group. Repeat X-ray and serum biomarkers will be performed at the 14 day and 45 day follow up timepoint.

[figure not shown]

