### 3.9 Follow up assessment data

Follow up will be at Day 14 ( $\pm$  2 days), day 42 ( $\pm$  2 days) and day 90 ( $\pm$  5 days) from date of recruitment. Data collected at these assessments will include:

- Attendance at follow up
- Mode of follow up assessment (i.e. in-person, telehealth (video) or telephone consult)
- Medication-related adverse events (see Appendix 3)
- Medication adherence assessment (see Appendix 4)
- Ulcer size
- Wlfl score
- Serum biomarkers (total peripheral white cell count, serum C-reactive protein)
- Changes to antibiotic therapy

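### Diarrhoea and nausea/vomiting count only if judged antibiotic-related, so background symptoms near day 42 count mainly in the 6-week arm and tilt a safety risk difference toward the short course, by an uncertain amount

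*Protocol*

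**What the plan says.** The Appendix 3 form has two gastrointestinal rows, and both make attribution a condition of the event. One reads "Diarrhoea: >3 loose stools per day associated with antibiotic administration in the absence of laxative or pre-existing enteritis"; the other reads "Nausea and vomiting: associated with antibiotic administration, in the absence of alternate explanation". Each item is scored yes or no for presence at the review. Section 3.9 has the form completed at days 14, 42 and 90 in both arms.

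Planned exposure differs by design. For the intervention, section 3.3 states "Patients will receive 2 weeks of antibiotic therapy from date of index X-ray demonstrating no radiological evidence of osteomyelitis"; section 3.4 gives 6 weeks for the control. The synopsis counts both durations from randomisation instead.

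The antibiotic-associated adverse event is one of four safety outcomes in section 2.3, where safety is part of the primary endpoint. The glossary defines it as a reaction to a prescribed antibiotic and names gastrointestinal intolerance as an example. Section 6.2 states the effect measure: "Exploratory clinical outcomes and safety outcome will be presented as risk difference with 95% confidence intervals".

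On masking, section 5.1 says "Serious adverse events will be referred to two independent clinicians blinded to the intervention". Section 3.10 masks investigators to follow-up X-ray results where feasible. Nothing is said about masking whoever completes Appendix 3.

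**The concern.** Whether loose stools or nausea can be tied to an antibiotic depends largely on whether the participant is taking one. At day 42 a control participant is at or near the end of a 6-week course. An intervention participant has been off planned antibiotics for about 28 days (42 − 14). The same background symptom is therefore likely to be scored yes in one arm and no in the other.

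The assessor would normally know which applies. No placebo is described, and the same review collects changes to antibiotic therapy and asks the Appendix 4 adherence questions.

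At stake is a safety contrast in the primary endpoint. Part of it could come from the attribution rule and not from harm, and section 6.1 says the pilot is to supply estimates for future trials. A symptom scored no because it was not attributed may leave no record, so the analysis could not reliably recover it.

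**Working it through.** **Plan's own figures.** The protocol gives no gastrointestinal event rate and no precision target for safety. Its one precision statement, an interval under 20% with 120 participants, reproduces: 2 × 1.96 × √(0.5 × 0.5/120) = 17.9%. It concerns feasibility only, and nothing below depends on it.

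**Inputs from the protocol.** Three reviews per arm (sections 3.5 and 3.9); courses of 2 and 6 weeks; 60 per arm. Nominally, one review (day 14) falls within or at the end of the short course and two (days 14 and 42) within or at the end of the long course.

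**Assumptions.** Background symptom prevalence *p* at each review, equal in both arms; no true drug effect; attribution probability *a1* on antibiotics and *a0* off; attribution judged separately at each review. A participant counts once if any review is scored yes.

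*Symptoms independent across reviews*
- 2-week arm: 1 − (1 − p·a1)(1 − p·a0)²
- 6-week arm: 1 − (1 − p·a1)²(1 − p·a0)

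At p = 5%:
- a1 = 1, a0 = 0: 5.0% v 1 − 0.95² = 9.75%
- a1 = 0.8, a0 = 0.1: 1 − 0.96 × 0.995² = 4.96% v 1 − 0.96² × 0.995 = 8.30%
- a1 = 0.6, a0 = 0.2: 1 − 0.97 × 0.99² = 4.93% v 1 − 0.97² × 0.99 = 6.85%

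*Symptoms persistent (the same participants affected at all three reviews)*
- 2-week arm: p[1 − (1 − a1)(1 − a0)²]
- 6-week arm: p[1 − (1 − a1)²(1 − a0)]
- Difference: p(1 − a1)(1 − a0)(a1 − a0)

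At p = 5%:
- a1 = 1, a0 = 0: 0, because everyone affected is already counted at day 14
- a1 = 0.8, a0 = 0.1: 0.05 × 0.2 × 0.9 × 0.7 = 0.63 points
- a1 = 0.6, a0 = 0.2: 0.05 × 0.4 × 0.8 × 0.4 = 0.64 points

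Spurious excess in the 6-week arm, in percentage points:

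| Attribution on/off | p = 2%, independent | p = 5%, independent | p = 10%, independent | p = 5%, persistent |
|---|---|---|---|---|
| 100% / 0% | 2.0 | 4.75 | 9.0 | 0 |
| 80% / 10% | 1.4 | 3.3 | 6.4 | 0.6 |
| 60% / 20% | 0.8 | 1.9 | 3.7 | 0.6 |

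**Sensitivity at p = 5%, independent, 100%/0%.** If 20% of the short arm is still on antibiotics at day 42, the 2-week risk is 1 − 0.95 × 0.99 = 5.95% and the gap falls to 3.8 points. If courses run from the index X-ray and end before the matching review, there are 0 versus 1 on-treatment reviews and the gap is 5.0 points.

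**Against sampling error.** At 5.0% v 9.75% with 60 per arm, the 95% half-width is 1.96 × √(0.05 × 0.95/60 + 0.0975 × 0.9025/60) = 9.3 points. The largest 5% figure in the table is about half of that.

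**Recording whatever the cause.** Background risk is the same in both arms: 1 − 0.95³ = 14.3% if independent, 5% if persistent. The spurious difference is 0.

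**The case against.** The strongest reply is that attribution is what this outcome means. The glossary defines it as a reaction to an antibiotic and section 3.9 calls the events medication-related, so the clause is consistent with the plan. That stands as a reason to keep the attributed outcome. It does not make the between-arm contrast unbiased when the judgement depends on the randomised exposure.

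Other points stand in part:
- The exclusions for laxatives, pre-existing enteritis and alternate explanations remove some background symptoms. They do not cover every cause of diarrhoea, and the last is itself a judgement.
- The one-versus-two count of on-treatment reviews is nominal. Sections 3.3 and 3.4 start the course at the index X-ray, the synopsis at randomisation, and reviews run from recruitment; these passages must be reconciled. Section 2.3 foresees antibiotics beyond the planned duration, which would narrow the gap.
- More true drug reactions over six weeks would be a real effect. Only the background part is bias.
- Section 6.2 specifies estimation, with no safety threshold, and the interval is wide beside the artefact.

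A reader might also infer more than the documents support:
- *That the assessors are stated to be unmasked.* The protocol never says open-label or names who attributes; this is an inference from the absence of placebo or masking and from the review questions.
- *That all other Appendix 3 rows, such as anaemia or creatinine, count in both arms at all three reviews whatever the cause.* Appendix 1 schedules no blood tests at day 90, section 3.9 lists only white cell count and C-reactive protein, and the glossary definition may govern those rows too.
- *That the bias is several points as a matter of fact.* With persistent symptoms it can be near zero.

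**Conclusion.** The point holds in limited form. The wording of the two gastrointestinal rows, with 2 versus 6 weeks of planned exposure and no described masking of allocation for this assessment, biases the antibiotic-associated adverse event risk difference toward the short course. The direction is firm provided attribution is likelier on antibiotics than off; none of the scenarios favours the long course.

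The size is not firm. At an assumed 5% prevalence per review it is about 0 to 0.6 points with persistent symptoms and about 1.9 to 4.8 with independent ones, before any reduction for the exclusion clauses or continued antibiotics in the short arm. The prevalence and the attribution probabilities are assumptions; the protocol supplies neither. This is a cheap improvement to data capture and reporting, not a flaw that invalidates the safety endpoint.

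**What to change.** In Appendix 3, take the attribution wording out of the diarrhoea and nausea/vomiting definitions. Record each symptom at every review in both arms whatever its cause, and add two fields: *on antibiotics at onset (yes/no)* and *judged antibiotic-related (yes/no)*.

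In section 6.2, report the between-arm risk difference for all-cause gastrointestinal symptoms to day 90 alongside the attributed antibiotic-associated outcome, and say that the attributed contrast is to be read with the attribution bias in mind.

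Do not replace the outcome with an any-cause composite of every Appendix 3 row. Peripheral neuropathy, anaemia and thrombocytopenia carry no baseline qualifier there, so pre-existing conditions would count in both arms and could hide real antibiotic harm.

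Cost: two reworded rows, two form fields and a sentence or two in section 6.2, with no extra visits or tests. The all-cause figure includes background events in both arms, so its interval is wider. At 14.3% in each arm the half-width is 1.96 × √(2 × 0.143 × 0.857/60) = 12.5 points, against 9.3 above.
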